### Participants

Participants for the qualitative study will be sampled from the cohort of smokers in S2 according to intensive sampling for theoretical representativeness and maximum variation. The selection criteria will be the dimensions from the 6-month follow-up questionnaire. The number of participants will be oriented towards meeting two requirements: that each testimonial has the potential to help understand the area/topic studied, and that the number of testimonials registered saturates the information collected. This threshold is met when participant themes are repeated. The selection criteria have been chosen to determine different profiles based on sex, age, main consumption, and smoking profile (previous quit attempts and receipt of help to quit smoking in the SUD program). Groups will be arranged according to four different dimensions of homogenization.

### Data collection and variables

We will conduct eight homogeneous discussion groups with 60 to 90-min duration. The sessions will be recorded and transcribed to preserve participants’ anonymity and confidentiality. During these sessions, two experts on qualitative research will explore the barriers and opportunities to quit smoking, experiences with the approach to smoking that participants received during their treatment for alcohol and/or cannabis use, and their opinion on the service received.

### Analysis

We will conduct a thematic categorical content analysis (TC-CA) applying the following rigor criteria suggested by Guba and Lincoln [49]: credibility, dependence, and confirmability.

### Ethical considerations

The research protocol has been submitted to and approved by the Clinical Research Ethics Committee (CREC) of the University Hospital of Bellvitge [PR315/20] and the CREC of each participating organization. Participants will receive a verbal explanation of the aims of the study and a written study information sheet, and will be asked to provide written informed consent. The ACT-ATAC project follows the standards of Law 3/2018 on the protection of personal data. The data collected in the computer application will be secure and will require personal passwords. The ACT-ATAC project is also registered at Clinicaltrials.gov [NCT04841655].

## Discussion

Over the course of the study, the COVID-19 pandemic forced us to adjust some parts of the study without changing its purpose or the core elements of its methodology. The most notable adjustment has been to replace face-to-face follow-up interviews with telephone-based interviews and to extend the study another year to ensure we recruit enough participants to have enough statistical power to conduct the analysis. All of the changes have been possible thanks to the successful collaboration between the coordinators, the clinicians, and the Public Agency of Public Health in Catalonia. The ACT-ATAC team has worked together in setting up multiple videocalls to keep the study on track.

In addition to the pandemic, another significant challenge faced by the ACT-ATAC research group was designing ad hoc baseline and follow-up questionnaires, particularly regarding the description of type of products and pattern of consumption for cannabis. Unlike the measurement for alcohol use, there are few validated questionnaires designed to monitor the consumption of cannabis (alone and in combination with tobacco). Therefore, we conducted a thorough review following recent recommendations [50–52] and developed a battery of questions to address the mode and frequency of consumption (i.e., marijuana, hashish, CBD oil) and its interaction with tobacco products in the past 30 days. The validity of these questions will be tested in the study and will be shared with the scientific community.

Moreover, we have included two scales used in the US to assess “Smoking-related Knowledge, Attitudes, and Services (KAS)” among users [42] and “Smoking-related Knowledge, Attitudes, and Practices (KAP)” [48] among providers. These scales were validated in the US, but their validity has not been assessed in Spanish. Therefore, we decided to translate them and validate their psychometric proprieties for the Spanish population. This work will allow us to have a valid Spanish language instrument to measure relevant variables in the tobacco control dimensions related to the views of users and staff. This validation is an added value for mental health professionals and decision-makers, as these scales could be of help in understanding how smoking cessation services are provided in SUD programs.

Furthermore, by describing individual and contextual predictors of tobacco use among alcohol and/or cannabis users treated for SUDs, we will better understand the factors that influence individuals to continue or quit smoking and the primary drug of use (alcohol and/or cannabis). Understanding which of these factors are associated with higher smoking and alcohol/cannabis cessation rates is key to informing the Spanish healthcare system’s future intervention programs based on the theory of change [53]. This would allow healthcare planners and stakeholders to design better evidence-based programs that consider the characteristics of the users and clinicians involved, helping to reduce the burden of smoking in this vulnerable population.

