**Discussion:**

The results of S1 were used to develop the questionnaires. S2 required some adjustments due to the COVID-19 pandemic, particularly the follow-up interviews being conducted by phone instead of face-to-face, and the recruitment rhythm was lower than expected. Recruitment will last until reaching at least 200–250 users. The fieldwork could not have been possible without the collaboration of the ACT-ATAC team and the introduction of several strategies.

***Trial registration*** The ACT-ATAC project has been successfully registered at Clinicaltrials.gov [NCT04841655].

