#### Sampling method

The incidence of unassisted smoking cessation is seven ex-smokers per 100 patient-years [33]. We estimate that, among this sample, being in contact with the health system may increase this rate to 10 ex-smokers per 100 patient-years (i.e., a relative risk [RR] of quitting smoking of 2.0). Therefore, to detect this RR assuming an alpha error of 5%, a beta error  < 20%, and losses of 20%, we require 366 participants. The sample size was calculated using the GRANMO program [34]. This sample size is achievable in one year as the 48 centers in the province of Barcelona treat approximately 5000 new cases for alcohol and 1500 new cases for cannabis yearly (target population: 6,500 participants) [12]. On average, the 10–12 selected study centers should treat approximately 1,625 people/year. Smokers in treatment for alcohol and/or cannabis use are being recruited consecutively for one year.

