#### Fieldwork and strategies implemented to overcome the barriers due to the COVID-19 pandemic

The longitudinal fieldwork kicked-off in November 2019 (month 11). The first step of the fieldwork was recruiting SUD centers and working clinicians willing to participate in the project. The pilot study was conducted between November 2019 and February 2020 and allowed us to test the recruitment process and software designed to collect and store data, as well as ensure the correct follow-up of participants. Nevertheless, in March 2020, the COVID-19 pandemic in Spain forced us to modify the follow-up interviews from face-to-face to telephone-based to limit the social contact of the research nurse with the participants. In addition, the rhythm of patient inclusion in the study slowed down from 1 or 2 per week before the lockdown (from March to June 2020) to 2 or 3 per month. Despite this, the study was able to be continue because the SUD centers in Catalonia remained open, though many of the visits were conducted online. Thus, the collaborating clinicians were still able to recruit patients who met the inclusion criteria during the pandemic; however, we recommended that they did so during in-person meetings to better assess participants’ cognitive status and make getting their informed consent easier. These adjustments were possible thanks to the collaboration between the study coordinators, the collaborating clinicians, and the Direction of the Substance Abuse Program at the Public Health Agency in Catalonia, that prioritized our project and contacted clinicians to keep this study on track despite the contextual circumstances. To increase the engagement of clinicians (clinical psychologists, psychiatrists, and nurses), we have conducted monthly online meetings with them to exchange experiences and difficulties in the recruitment process and given them a certificate of participation in the study signed by the Director of the Substance Abuse Program at the Public Health Agency in Catalonia and the Principal Investigator. These meetings are an informal 30-min coffee break in which investigators and clinicians get together and share their experiences regarding the recruitment process and present the latest information on the participants’ profile. A mug with the main inclusion and exclusion criteria has been designed and gifted to clinicians for them to pick up during these meetings (Fig. 3).

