**Fig. 3 Fig3:**
[figure not shown]
Clinician’s mug with the inclusion and exclusion criteria

Moreover, to improve participants’ fidelity in the follow-up study, halfway through the study, we started offering 20 euros gift cards to those who answer all of the phone calls during the 12-month follow-up. At the time of submitting this manuscript, 98 patients have been recruited. Thus, we will continue the study until we recruit at least 200 to 250 participants (expected by the end of 2022).

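### The Discussion says the extension secures enough statistical power, but the goal was lowered from 366 to at least 200–250 with no new calculation, and on stated assumptions power for abstinence at RR 2.0 is about 30–36%

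*Protocol article*

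**What the plan says.** Sampling method gives the requirement. It sets the reference rate ("The incidence of unassisted smoking cessation is seven ex-smokers per 100 patient-years"), the expected rate ("being in contact with the health system may increase this rate to 10 ex-smokers per 100 patient-years") and the effect to detect ("a relative risk [RR] of quitting smoking of 2.0"). With alpha 5%, beta below 20% and "losses of 20%, we require 366 participants", the number reads as a total for the cohort of smokers.

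The section on fieldwork during the pandemic reports 98 patients recruited and says the study continues "until we recruit at least 200 to 250 participants", which it expects by the end of 2022. The abstract agrees: "Recruitment will last until reaching at least 200–250 users". Neither place revises the effect size, alpha, power or loss assumption.

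The Discussion describes the extension as a decision "to extend the study another year to ensure we recruit enough participants to have enough statistical power to conduct the analysis", and says the pandemic adjustments left the core of the methodology unchanged. Limitations and strengths does not mention power.

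Statistical analysis compares participants who did and did not receive cessation support. It uses Poisson regression with robust variance, reports RRs with 95% CIs and sets significance at p < 0.05. Abstinence and quit attempts are both called primary outcomes there.

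**The concern.** The article prints a required number, a recruitment goal that is 55–68% of it (200/366 and 250/366), and an assurance of sufficient power. These cannot all stand unless some design assumption changed, and none is reported as changed. This is not a detail left to an analysis plan, because all three statements are in the article.

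At stake is how the results for aim 3, the predictors of cessation, will be read. A reader who accepts the assurance would take a non-significant RR for abstinence as evidence that cessation support, or another predictor, makes no difference. With 160–200 evaluable patients and 10% abstinent, only 16–20 abstainers are expected, so a true doubling would more often than not be non-significant.

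**Working it through.** **Inputs from the article.** Reference 7 and expected 10 per 100 patient-years; RR 2.0; alpha 5%; beta below 20%; losses 20%; N = 366 (Sampling method). Goal at least 200–250, with 98 recruited (fieldwork section). Status date December 2021 (Design). Comparison by receipt of cessation support (Statistical analysis).

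**Assumptions, because the article is silent.** 7 per 100 patient-years is taken as a 7% risk at 12 months, so RR 2.0 means 7% versus 14%. The test is two-sided, since 95% CIs are reported. Exposure is split 1:1, with 20–70% exposed shown as a range.

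**Step 1: reproduce 366.** Arcsine formula, per group: n = 2[(1.960 + 0.842)/h]², with h = 2·arcsin√0.14 − 2·arcsin√0.07 = 0.2315. This gives n = 293, and 293/0.8 = 366. The plan's figure is matched, but as a per-group size. The pooled normal formula gives 300 per group and 300/0.8 = 375. As a total, 7% versus 14% needs about 733–750. The stated 7 versus 10 is a ratio of 10/7 = 1.43, not 2.0, and would need about 3,370–3,555 in total.

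**Step 2: power for abstinence at the goal.** Power = Φ[(|p1 − p0| − 1.96·s0)/s1]. Here s0 = √[p̄(1 − p̄)(1/n0 + 1/n1)], p̄ is the pooled proportion, and s1 = √[p0(1 − p0)/n0 + p1(1 − p1)/n1].
- N = 200, 160 evaluable, 80 per group: s0 = 0.0485, s1 = 0.0482; (0.07 − 0.0950)/0.0482 = −0.519; power 30%.
- N = 250, 200 evaluable, 100 per group: s0 = 0.0434, s1 = 0.0431; (0.07 − 0.0850)/0.0431 = −0.348; power 36%.
- N = 366 in total, 293 evaluable: power about 50%.

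**Step 3: vary the assumptions at N = 200 and 250, with 20% losses.**

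| Scenario | Power at 200 | Power at 250 |
|---|---|---|
| 7% v 14%, 20% exposed | 28% | 33% |
| 7% v 14%, 30% exposed | 31% | 37% |
| 7% v 14%, 70% exposed | 21% | 26% |
| 5% v 10%, 1:1 | 22% | 27% |
| 10% v 20%, 1:1 | 42% | 51% |
| 7% v 10%, 1:1 | 10% | 12% |

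**Step 4: take 366 in total at face value as giving 80%.** Power = Φ[2.802·√(N/366) − 1.960], which is 54% at 200 and 64% at 250.

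**Step 5: detectable RR and precision (1:1, 7% reference).** The exposed risk detectable with 80% power is 22.6% at N = 200 (RR 3.2) and 20.6% at N = 250 (RR 2.9). For a true RR of 2.0, SE(log RR) = √[0.86/(0.14m) + 0.93/(0.07m)], with m per group. This is 0.493 at m = 80 and 0.441 at m = 100. The expected 95% CIs, 2·exp(±1.96·SE), are about 0.76–5.3 and 0.84–4.7.

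**Step 6: accrual.** About 12 months remain to the end of 2022. The goal needs (200 − 98)/12 = 8.5 to (250 − 98)/12 = 12.7 enrolments a month. The article reports a fall from 1 or 2 a week "to 2 or 3 per month". The average since November 2019 is 98/26 to 98/25, or 3.8–3.9 a month. At 2 a week, the top of the pre-lockdown range, 98 + 104 = 202.

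**The case against.** **The power figure is conditional.** This stands. The article gives neither the exposure split nor the sidedness, so 30–36% must be printed with its assumptions. The conclusion does not depend on them: no two-group abstinence scenario checked at 200–250 reaches 80%.

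**The reduction is not the whole cause.** This stands. A reader might infer that lowering the goal took power from 80% to 30–36%. By the same method 366 in total already has about 50%, so the reduction explains a fall from about 50%. Taken at face value, the plan's own number leads to 54–64%.

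**Another test would be powered.** A one-sample test of 14% against a fixed 7% would have 87–92% power with 160–200 evaluable. That reading needs 162 participants after losses, not 366, and is not the comparison in Statistical analysis.

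**Quit attempts are also primary.** This stands. The article gives no quit-attempt rate. If 20–30% of unexposed patients made an attempt (an assumption), RR 2.0 would have about 79–99% power at 80–100 per group. A reader might infer that every analysis is underpowered; the documents support the shortfall for abstinence only.

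**The goal is a floor and the date an expectation.** Both are true, but no higher goal is stated. A reader might also infer that no reported accrual rate reaches the goal; 2 a week just reaches 200, though not 250. A firm projected total is not supported either. One or two a week over the pilot (about 17–35 patients) followed by 2 a month for 22 months gives 61–79, not the 98 reported.

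**Significance testing.** A reader might conclude that p < 0.05 should be abandoned. That would be a preference, since RRs with 95% CIs are already planned.

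**Conclusion.** The assurance of sufficient power in the Discussion is not supported for abstinence and conflicts with the article's own requirement. Power for RR 2.0 at the current goal is about 30–36% under 7% versus 14%, a 1:1 split, two-sided 0.05 and 20% losses. It is about 21–37% if 20–70% are exposed, and 10–12% for the two rates the plan states. The reading most favourable to the plan's own number, 366 in total as 80%, still leaves 54–64%.

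Two defects in Sampling method compound this. The figure 366 fits its inputs only per group, and RR 2.0 does not follow from 7 and 10 per 100 patient-years. The accrual shortfall is secondary: it bears on the expected date, not on whether the power statement is true.

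**What to change.** 1. In the Discussion, remove or correct the statement that the extension ensures sufficient power.
2. Where 200–250 is given, call it a feasibility target below the original requirement.
3. In Sampling method, say whether 366 is per group or in total, and reconcile RR 2.0 with 7 versus 10 per 100 patient-years.
4. Report, with their assumptions, the power for abstinence at 200–250, the detectable RR (about 2.9–3.2) and the expected 95% CI for a true RR of 2.0 (about 0.76–5.3 at 200, 0.84–4.7 at 250).
5. In Limitations and strengths, list low power for abstinence and say that a non-significant RR will not be read as no association.
6. Revise the end-2022 expectation, or state the accrual rate it relies on.

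The cost is wording only: no change to design, data collection or analysis method. The price is a less favourable stated power.

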## Limitations and strengths

A key study limitation may be the limits on extrapolating the findings, as it is complex to understand the use of tobacco and other drugs in a way that represents all SUD clinicians and patients, and we do not know the extent to which the pandemic has affected the attendance of SUD programs. However, the mixed methods design includes several heterogeneous discussion groups for both clinicians and patients with different broad typologies in order to capture a broad range of experiences, barriers, and opportunities and how the pandemic has impacted them. Regarding the questionnaires, self-reported data may include reporting or cognitive biases from participants. Moreover, on account of the patient-professional relationship, selection bias is possible among recruiting clinicians, who could offer the study only to patients who they believe will agree to participate. Lastly, conducting the follow-up interviews by telephone instead of face-to-face may affect the quality of the data collected. However, we had no other option due to the COVID-19 pandemic.

Despite its limitations, the study includes a mixed methods exploratory approach, represents both patient and clinician perspectives, permits triangulation of multiple data sources, and measures primary outcomes (abstinence and quit attempts) in a 1-year follow-up design.

Finally, we strongly believe that the adjustments that were made have allowed us to carry out the study despite the pandemic. Complex observational studies allow the study of real-life phenomena; however, researchers may need to overcome difficulties, such as the COVID-19 pandemic, by introducing innovative strategies to successfully carry out these studies [54]. We are confident that studying tobacco use among the SUD population under these circumstances will allow us to design programs that can be sustained in the real life of clinicians and patients.

## Data Availability

Not applicable.
